### Sample size calculation

We estimated the sample size needed for this study using the statistical power of a hypothesis test using the Python module statsmodels [32]. We considered the following parameters:Level of significance (α) = 0.05Statistical power (1-β) = 0.8Effect size (Cohen's d) = 0.6

The required number of patients was 45 per group. Therefore, considering that we aim to compare patients who will show a progression to objective cognitive decline and patients who will not, the total estimated sample size should be 90 individuals.

With an expected conservative drop-out rate of 10%, the number of participants to be included was estimated to be 99 patients.

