### Machine learning classification of patient conditions

Demographic, clinical, cognitive, neurophysiological, and genetic data will be used as candidate input features without any further processing for training a machine learning model. During the training process, a feature selection algorithm will be applied to select the most informative features based on their performance on the validation set.

The machine learning problem will initially be treated as a multi-class classification task. The model will classify patients who are SCD at the time of the measurements into one of the following three classes: stable SCD, progressed to MCI, or progressed to AD dementia. For the subgroup of patients undergoing CSF biomarker analysis, a classification will be performed based on the results of the analysis. Specifically, patients will be classified as carriers or non-carriers of AD pathology, according to the NIA-AA framework [9].

For feature selection, we will test the efficacy of several algorithms including the ANOVA F-test statistic, ReliefF, mutual information, and minimum redundancy maximum relevance (MRMR). The number of retained features for each algorithm will be optimized in the validation loop.

Regarding the classifier models, a set of different machine learning models will be tested, including support vector machine (SVM) with linear, quadratic, cubic, and radial basis function kernels; random forest (RF); gradient boosted trees (xgboost); linear and quadratic discriminant analysis (LDA and QDA); and an artificial neural network (ANN). The hyperparameters of each algorithm will be optimized to determine the model with the best performance in the classification task.

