In the SVM, the parameters C (misclassification penalty) and gamma (influence of single training points) will be optimized. For the RF, the number of trees (estimators), maximum depth of each tree, and minimum number of data points allowed in a leaf node will be optimized. The same hyperparameters will be tuned for xgboost, along with the learning rate of the algorithm. In LDA and QDA, the type of solver used by the algorithm and the shrinkage term will be adjusted. For the ANN, the number of layers and neurons per layer will be optimized. We have chosen to compare feature selection methods from classical statistics (such as ANOVA F-test) with data-driven methods (ReliefF and MI) that do not assume the distribution of the data. Additionally, the MRMR algorithm will be tested to consider possible redundancies among features.

In the machine learning models, both linear (linear SVM and LDA) and non-linear (polynomial and radial basis function [RBF]-SVM and QDA) algorithms that define separating hyperplanes will be tested, along with tree-based methods like RF and xgboost. The ANN will serve as a non-linear, black-box model to assess the discrimination performance and potential overfitting of more complex models. Furthermore, standard dimensionality reduction techniques will be applied to extract the most salient features. The procedure described above will be repeated to evaluate whether similar results can be achieved with a subset of the features. Once the cross-sectional classification is performed, longitudinal data will be utilized to develop an algorithm capable of predicting the future progression of cognitive impairment.

Out of the entire dataset, 30% of the data will be reserved as a testing set, while the remaining 70% will be used for training and validation of the model. A fivefold cross-validation approach will be employed to train and optimize the hyperparameters of the models. The best performing model, determined by the prediction F1-score and the set of optimized hyperparameters, will be tested on the testing set to obtain an unbiased estimate of the model's performance.

A visual summary of the data collection and analysis process is shown in Fig. 2.

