This approach offers several advantages over classical statistics. Firstly, it allows us to consider all the collected variables simultaneously. Secondly, the machine learning procedure helps identify the most informative features for screening, enabling the development of a protocol that reduces the burden on patients and healthcare costs associated with cognitive assessments.

Furthermore, this approach will provide additional evidence to clarify the role of certain variables that still have controversial associations with SCD. For example, numerous studies have shown that individuals with SCD have lower scores on neuropsychological tests compared to those without SCD [78–80]. However, only a few longitudinal studies have assessed the prognostic value of baseline neuropsychological assessments, often yielding conflicting results [81–84].

Several studies have focused on the relationship between SCD and cognitive reserve [85–89]. Engaging in intellectual activities during earlier decades and having higher premorbid intelligence have been identified as protective factors, reducing the risk of progression from SCD to MCI [15, 16]. However, cognitive reserve seems to have a dual effect, as individuals with higher cognitive reserve exhibit faster disease progression once it begins [16, 90]. The interaction between SCD and mood disorders is also controversial. Recent community-based studies on large populations have shown that depressive symptoms increase the risk of progression to objective cognitive decline and dementia in SCD patients [91, 92]. However, a meta-analysis by Huang et al. found that depression was significantly higher in individuals with SCD compared to normal individuals, but there was no difference between SCD and MCI, or between SCD converters and non-converters [93]. Studies on personality traits have yielded conflicting results regarding their association with SCD. Most studies agree that high conscientiousness and low neuroticism are associated with a reduced risk of incident AD [94, 95]. However, a previous study found that emotional stability was significantly higher in SCD patients who progressed to MCI or AD dementia [96].

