## Conclusions

The advent of DMTs will bring about a significant shift in the management of patients with cognitive decline caused by AD. Since the efficacy of these drugs is closely tied to the disease stage, it is crucial for clinicians to be able to identify individuals at risk of AD before neurodegeneration sets in. A suitable target population for this purpose is individuals who present with cognitive complaints but lack objective evidence of impairment. The PREVIEW study aims to extensively characterize patients with SCD through clinical, neuropsychological, neurophysiological, and genetic assessments. Utilizing a machine learning approach, we aim to assess potential biomarkers and develop a robust predictive model to evaluate the risk of progression to AD. This approach will provide relevant evidence regarding the most significant features to be assessed as the initial step in the diagnostic pathway for patients with SCD, before confirming the presence of AD pathology through more invasive and expensive tests.

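### The selected features are an intended product of the study, but the single 70/30 split tests only the model's prediction and gives no evidence that those features are reproducible

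*Protocol article*

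**What the plan says.** Under *Machine learning classification of patient conditions*, the protocol article states that "a feature selection algorithm will be applied to select the most informative features based on their performance on the validation set". Four selectors are named (ANOVA F-test, ReliefF, mutual information, MRMR), and the number of features kept is tuned. Several classifiers are compared and the best by F1-score goes forward. On the data split: "30% of the data will be reserved as a testing set, while the remaining 70% will be used for training and validation of the model". On the inner loop: "A fivefold cross-validation approach will be employed to train and optimize the hyperparameters of the models". The 30% set is then used once, to estimate the performance of the winning model.

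The selected features are meant to be used. The third aim in the *Background* is a management protocol for memory clinics. The *Discussion* says that "the machine learning procedure helps identify the most informative features for screening" and links this to a shorter assessment protocol. The *Conclusions* state: "This approach will provide relevant evidence regarding the most significant features to be assessed as the initial step in the diagnostic pathway".

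Under *Sample size calculation*: "The required number of patients was 45 per group", so that "the total estimated sample size should be 90 individuals".

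**The concern.** The study makes two kinds of claim: how well a model predicts, and which features matter. The test set supports the first only. A model can predict acceptably while several of its selected features are there by chance, because the true predictors beside them carry the prediction. A good test-set F1-score therefore does not vouch for the list, and this is so even when real predictors exist.

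Fivefold cross-validation is described for training and tuning, not for recording how often each feature is chosen. The planned repeat with a subset of features asks whether fewer features predict as well; it does not rerun the selection on other samples. As written, features could be put forward for a screening or management protocol with no measure of how far their selection depended on which patients fell into the training set.

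**Working it through.** **1. The article's own figure.** A two-sided two-sample t-test with d = 0.6, alpha = 0.05 and power 0.80 needs 44.59, hence 45 per group and 2 × 45 = 90 in total. The stated figure reproduces. It is sized for one two-group comparison, not for picking features from many.

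**2. Patients available for selection.** 0.70 × 90 = 63 for training and validation; 0.30 × 90 = 27 for testing.

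**3. Candidate features.** The total is not stated. What can be counted: 4 bands × 6 regions = 24 spectral powers, about 25 test and scale scores, 5 personality traits, 3 activity domains and 2 genes. That is about 59 before network, microstate and ERP features. Assumption: 100 to 150, with 200 as a sensitivity case.

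**4. Check by hand.** With 63 patients split equally, a true feature at d = 0.6 has a typical t of 0.6 × √63 / 2 = 2.38. A noise feature exceeds this in absolute value with two-sided probability of about 0.02 (61 df). Among 90 to 140 noise features, that is about 90 × 0.02 = 1.8 to 140 × 0.02 = 2.8. So about five of ten true features and two to three noise features lie above 2.38, and the remaining two to three places are contested by five true features and nearly all the noise.

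**5. Simulation.** Assumptions: ten independent true predictors at d = 0.6, 100 to 150 candidates, 90 patients, 30-50% progressors, F-test ranking, top 10 kept, 600 runs per setting.

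| Comparison | Features (of 10) | Reading |
|---|---|---|
| Shared by two 70% draws of the same 90 patients | 5.3 to 6.1 | 10 − 6.1 = 3.9 to 10 − 5.3 = 4.7 change |
| Shared by two independent cohorts | 2.8 to 4.1 | 5.9 to 7.2 change |
| Noise features in one list | 3.7 to 4.9 | about 4 to 5 |

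**6. List size tuned by fivefold cross-validation, closer to the plan** (d = 0.6; 100 and 200 candidates). With 45 progressors and 45 non-progressors, 60% and 55% of the list recurs on a re-split, and 43% and 34% in a new cohort; 55% and 49% of the features are genuine. With 18 and 72 (an assumed imbalance), 58% and 48% recurs on a re-split, and 35% and 21% in a new cohort.

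**7. Sensitivity to effect size** (top 10, 45/45, 100 to 200 candidates):

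| d | Recurs on re-split | Recurs in new cohort |
|---|---|---|
| 0.4 | 48% to 39% | 19% to 12% |
| 0.6 | 60% to 53% | 38% to 29% |
| 1.0 | 87% to 82% | 82% to 75% |

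The stability at d = 1.0 also needs enough progressors: with 18/72 and 200 candidates it falls to 71% on a re-split and 53-56% in a new cohort.

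**8. Effect of resampling** (d = 0.6). Features chosen in at least 60% of bootstraps of the training set are 80-90% genuine, against about 51-63% for the single list. In a separate run that bootstrapped all 90 patients (45/45; 100 and 200 candidates), the 60% threshold kept about 4.5 and 3.4 features (94% and 91% genuine), and an 80% threshold kept 2.2 and 1.6 (98% genuine). Across the class balances tried, the share of the 60% list found again in a second cohort was only 0.17 to 0.40.

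**The case against.** **A condensed article.** A fuller plan may contain a stability step, and silence alone would not be a finding. That is fair, and such a step may exist. But the article does set out selectors, classifiers, tuning, split and winner rule, and draws pathway claims from them. What it describes does not support those claims.

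**The plan is richer than one selection.** Several selectors are compared within fivefold cross-validation, MRMR is included to deal with redundancy, and the split is not described as random. All correct. None of it measures whether the chosen features recur.

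**The wording is cautious.** The article speaks of evidence and of helping to identify features; nowhere does it commit to adopting the raw list unexamined. This stands. A reader might infer that features will enter the diagnostic pathway purely because of how the data happened to be split. The text does not go that far.

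**The inputs are assumed.** The d = 0.6 is a sample-size input, not a per-feature effect. The number of candidates, their independence, the number of true predictors and the two-class outcome are also assumptions, and the outcome actually planned has three classes. This stands too: the figures illustrate a range and do not forecast this study's result.

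**The remedy does not make cohorts agree.** True. Disagreement between cohorts reflects 90 patients, and resampling cannot change that.

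**Conclusion.** The point holds in limited form. The plan would name informative features from the best pipeline on one 70/30 split of about 90 patients, with a check on prediction and none on the reproducibility of the features. Under the assumptions in the working at d = 0.6, about 40-47% of a top-10 list changes on a re-split, about 60-70% changes in a new cohort, and about 4 to 5 of 10 features are noise. Weaker effects make this worse; at d = 1.0 with balanced groups the list is largely stable.

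A reader might infer that merely re-splitting the same patients would give a largely different list. The figures do not support that: at d = 0.6 with 100 to 150 candidates, more than half the list recurs. Largely different fits a new cohort only, and only if effects are moderate or weak.

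**What to change.** Repeat the whole selection procedure, including the choice of selector and the number of features kept, over many bootstrap or repeated stratified resamples of the training data. Report how often each feature is selected, counting a group of highly correlated features as one. Base any recommended list on a frequency threshold that the sponsor chooses and fixes in advance. The choice matters: in the runs above, 60% kept roughly twice as many features as 80%, at a small loss of purity. Keep the 30% test set for its present purpose.

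The cost is computing time and a paragraph of text; no further patients, visits or data are needed. The list will be shorter and may be empty. It will be purer and will show how few features 90 patients can support, but independent cohorts may still select different ones. The Discussion and Conclusions should therefore present the features as candidates for confirmation.

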## Methods and analysis

### Study design and participants

This is a longitudinal observational cohort study. We will include consecutive patients who self-referred to the Centre for AD and Adult Cognitive Disorders of Careggi Hospital in Florence and are classified as SCD based on SCD-I criteria [5].

We will recruit patients who meet the following criteria:

Iage between 45 and 90 years;IIcomplaining of cognitive decline with a duration of ≥ 6 months;IIIMini Mental State Examination (MMSE) score greater than 24, corrected for age and education;IVnormal functioning on the Activities of Daily Living (ADL) and the Instrumental Activities of Daily Living (IADL) scales [28];Vunsatisfied criteria for MCI [29] and dementia [30];

Exclusion criteria are history of head injury, current neurological and/or systemic disease, symptoms of psychosis, major depression, or substance use disorder (as defined by the Diagnostic and Statistical Manual of Mental Disorders, Fifth Edition [DSM-5] [30]).

The evaluation of exclusion criteria will be conducted through a thorough neurological examination of the patients. The presence of exclusion criteria will be assessed by two independent neurologists. In the event of a disagreement, a third neurologist will be consulted to reach a consensus.

All recruited patients will undergo the following assessments at baseline (T_0_):Icomprehensive evaluation of familial and clinical history;IIextensive neuropsychological assessment, including estimation of premorbid intelligence, evaluation of depression, personality assessment, and assessment of leisure activities;IIIblood collection for measurement of vitamin B12, folic acid, thyroid hormones, as well as *APOE* and *BDNF* genotype analysis;IVEEG and ERP recording.

Patients who provide additional informed consent for lumbar puncture will undergo CSF collection to measure Aβ_42_, Aβ_42_/Aβ_40_ ratio, total tau (t-tau), and phosphorylated tau (p-tau).

Patients will undergo neuropsychological evaluations every two years until progression to AD or other dementias. Based on the results of previous meta-analysis [8], we estimate that a period of six years will be required to reach the desired sample size (see Sect. 2.2). Progression to MCI and AD dementia will be determined based on the criteria established by the NIA-AA [29, 31]. Patients who progress to dementia will be referred to our centre for diagnostic and therapeutic assessments.

A summary of the study design is shown in Fig. 1.

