The PREVIEW study also has several strengths that deserve emphasis. As mentioned earlier, the use of machine learning is a significant strength and the primary innovative outcome of our project. Another strength is the collection of AD CSF biomarkers, which serves two main purposes: i) given that previous studies have reported an average ten-year period for SCD patients to develop dementia [8, 96], a long follow-up will be necessary to obtain an adequate sample size of patients who progress to AD. By using CSF biomarkers, we can identify patients at a higher risk of AD dementia (according to the ATN system [9]) and classify them as prodromal AD. This classification can be considered as a surrogate target for preliminary cross-sectional analyses; ii) as mentioned earlier, SCD can also be the first clinical manifestation of medical conditions other than AD. CSF biomarkers will enable us to differentiate SCD with Alzheimer's pathology from SCD due to other causes. It should be noted that our study includes patients who self-refer to our memory clinic, as recommended by previous studies, to reduce sample heterogeneity and increase the chances of identifying subjects with preclinical AD compared to community-based studies [116]. Finally, we would like to emphasize that all the features considered as potential predictors will be derived from non-invasive, relatively inexpensive, and easily accessible techniques.

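### The three outcome classes have no time point and no minimum follow-up for stable SCD, so the label partly reflects how long each patient has been observed

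*Protocol article*

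**What the plan says.** All references are to the Protocol article.

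- **Target.** Machine learning classification of patient conditions states: "The machine learning problem will initially be treated as a multi-class classification task". Patients who have SCD when measured are to be placed "into one of the following three classes: stable SCD, progressed to MCI, or progressed to AD dementia". No date, visit or minimum observation time is attached to any class, and there is no class or rule for a patient whose status is not yet known.
- **Models.** The same section lists ordinary classifiers (support vector machines, random forest, boosted trees, discriminant analysis, a neural network). The winner is chosen by F1-score in cross-validation and then scored on a reserved 30% test set.
- **Entry and follow-up.** Study design and participants says "We will include consecutive patients who self-referred to the Centre for AD and Adult Cognitive Disorders", and then "Patients will undergo neuropsychological evaluations every two years until progression to AD or other dementias".
- **Six years.** The same section adds "we estimate that a period of six years will be required to reach the desired sample size".
- **Later step.** After the cross-sectional classification, "longitudinal data will be utilized to develop an algorithm capable of predicting the future progression of cognitive impairment". No method or horizon is named.
- **Latency.** The Discussion notes that "previous studies have reported an average ten-year period for SCD patients to develop dementia". It offers CSF status as a surrogate target for preliminary analyses.
- **Drop-out.** This appears only under Sample size calculation, as a 10% increase from 90 to 99 patients.

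**The concern.** Consecutive entry and open-ended two-yearly visits mean that observation time differs between patients at any data cut. A patient unchanged at year 2 and another unchanged at year 6 receive the same label, although the first has been ruled out as a progressor for only a third as long. MCI and AD dementia are successive stages, so the boundary between those two classes also moves with the date of analysis.

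Three things are at stake:

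- Future progressors sit in the comparison class. This lowers the apparent progression rate and pulls predictor effects towards zero.
- The 30% test set carries the same labels as the training set. Its F1-score describes agreement with the label at the data cut, not with true progression, so holding the set out does not remove this bias.
- A predicted probability of progressing has no time attached, which makes it hard to build into the management protocol of aim iii.

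**Working it through.** **1. The plan's own figure.** A two-sided two-sample t-test with d = 0.6, alpha 0.05 and power 0.80 needs 44.59, so 45 per group, as stated. Then 2 x 45 = 90, and 90 x 1.10 = 99. The figure reproduces. It compares progressors with non-progressors, again without a time point, so the issue lies in the label and not in the arithmetic.

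**2. Mislabelling with follow-up of 2, 4 and 6 years.** Assumptions, none from the article: constant hazard; one third of patients at each length of follow-up; true 6-year progression F of 30% or 50%.

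- Hazard: lambda = -ln(1 - F)/6.
- Observed share: P = mean of 1 - exp(-lambda t) over t = 2, 4, 6.
- Share of 6-year progressors labelled stable: 1 - P/F.
- Their share of the stable class: c = (F - P)/(1 - P).
- Attenuated effect: 0.6 x (1 - c). This assumes that missed progressors have the same feature mean as observed ones.

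| | F = 0.30 | F = 0.50 |
|---|---|---|
| Progressed by 2, 4, 6 years | 0.112, 0.212, 0.300 | 0.206, 0.370, 0.500 |
| Observed share P | 0.208 | 0.359 |
| 6-year progressors labelled stable | 1 - 0.208/0.300 = 31% | 1 - 0.359/0.500 = 28% |
| Share of the stable class | 0.092/0.792 = 12% | 0.141/0.641 = 22% |
| d = 0.6 becomes | 0.53 | 0.47 |

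With 45 per group, power falls from 80% to about 70% and 59%.

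**3. Uniform entry over six years.** If patients enter evenly over six years and the data are cut at the end of that time, completed two-yearly follow-up is 0, 2 or 4 years for one third each. A simulation with an average hazard of 5-10% per year and one true predictor gave:

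- 60-63% of 6-year progressors labelled stable.
- Observed progression 9-15%, against a true 24-39% at six years.
- AUC of the true predictor 0.71 against the observed label, and 0.73-0.75 against true 6-year status.
- Follow-up length alone separates progressed from stable with AUC 0.74-0.75.

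Part of the 60% comes from the third of patients who have no follow-up visit. If they are left out, half the remainder have 2 years and half 4. The constant-hazard figures above then give 1 - 0.162/0.300 = 46% (F = 0.30) and 1 - 0.288/0.500 = 42% (F = 0.50).

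**4. Does the model learn follow-up length?** In the same simulation, a feature with no prognostic value has AUC 0.50 for the observed label when it is unrelated to follow-up. It reaches 0.61-0.62 only when a correlation of 0.5 with follow-up is imposed.

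**5. The article's own latency.** Take ten years as the mean time to dementia among eventual converters. The share converted by six years is 1 - exp(-6/10) = 0.45 for an exponential distribution, and 0.34 and 0.22 for gamma distributions with shape 2 and 4. So 55-78% of eventual converters would not yet be labelled AD dementia even after a full six years.

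**The case against.** **This is a condensed article, and classification is only the initial step.** A full protocol or analysis plan could hold the data-cut rule and the method for the longitudinal algorithm. This stands for the longitudinal step: one summary sentence is no evidence that the plan ignores censoring there. It does not rescue the three-class target, which the article itself fixes, together with classifiers and a selection metric that, as described, make no allowance for incomplete follow-up.

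**The article supplies six years and a CSF surrogate.** The six years can be read as a planned span for outcomes to accrue, but it is tied to reaching the sample size and not to each patient's label. The CSF target needs no follow-up, but it covers only patients who consent to lumbar puncture and does not alter the three classes.

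**Stronger readings.** A reader might infer that drop-outs are labelled stable. Nothing in the article says so, and the step from 90 to 99 fits equally well with leaving them out, which would be an unstated complete-case choice. A reader might also infer that the model learns length of follow-up. Neither follow-up length nor recruitment date is among the listed inputs, so this happens only if included features correlate with follow-up, and the article gives no evidence on that.

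**The magnitudes are assumed.** This stands. Two plausible entry patterns differ about twofold in the mislabelled share.

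**Conclusion.** The concern holds for the class definition. As written, retained patients with short follow-up can only be labelled stable SCD, and the split between MCI and AD dementia depends on when the analysis is run. The label therefore partly reflects length of follow-up, in the training and test sets alike. Even if no feature correlates with follow-up, progression is understated, predictor effects are attenuated and the held-out F1-score is biased for true progression.

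The size is illustrative only: about 28-31% of 6-year progressors mislabelled with follow-up spread evenly over 2, 4 and 6 years, and about 60% with uniform entry over six years. Hazards, entry patterns and distribution shapes are assumptions. The direction of the bias does not depend on the particular values chosen, and the ten-year average quoted in the Discussion makes it unlikely to be negligible. How drop-outs are handled is simply not stated.

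**What to change.** - **Define the classes at a fixed horizon**, for example the third two-yearly visit (6 years): stable SCD, MCI or AD dementia by status at that visit. Stable should require follow-up to the horizon.
- **Do not simply drop stable patients with shorter follow-up while keeping early progressors.** In step 2 with F = 0.30, that would leave 0.208 progressors against 0.700/3 = 0.233 stable patients, an apparent progression of 0.208/0.441 = 47% instead of 30%.
- **Handle patients not observed to the horizon** by inverse-probability-of-censoring weights, or by a discrete-time multi-state or cause-specific hazard model on the visit intervals. Keep all records of one patient in the same fold and on the same side of the 70/30 split.
- **Keep MCI and AD dementia as separate outcomes**, as aim ii does. A single binary progression target would merge them.
- **Treat death and non-AD dementia as competing events**, and state how drop-outs enter the analysis.
- **Report censoring-adjusted performance at the horizon**: time-dependent AUC and Brier score.

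The change is to analysis wording and code, not to visits or recruitment, provided that visit dates are recorded (the article does not say). It is best made before labels are assigned. The costs are more analysis work, results tied to one horizon, and few AD dementia events by that time.
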